## **5.2 Biobank study**

Only participants providing specific separate consent will be enrolled in the biobank study. We will collect blood samples from patients at baseline, i.e. before and after starting the NACT and/or before surgery, and then at 28 days after surgery, 6 months and 12 months. We will collect serum, and obtain 1 EDTA whole blood tube for DNA analysis, and 1 RNA PaxGene tube for blood RNA analysis. Samples will be stored at  $-160^{\circ}\text{C}$  in liquid nitrogen vapour.

## **6. STATISTICAL ANALYSES**

### **6.1 Primary Analysis**

The primary analysis will compare the performance of preoperative frailty assessment based on the FP and perioperative cardiovascular risk assessment based on the combination of preoperative RCRI, age and occurrence of MINS, in predicting the composite of all-cause death or new disability at 6 months after surgery. We will assess the association of FP and of RCRI+age+MINS with the primary outcome using logistic regression models. We will perform one logistic regression model including frailty as predictor, and one logistic regression model including the baseline RCRI+age+MINS as predictors. For each model we will then calculate the c-statistics (corresponding to the AUROC) and compare them using a non-parametric approach. We will include in the primary analysis only study participants who are alive at 28 days after surgery. We expect this will exclude from the primary analysis a very small proportion of patients initially enrolled in the study (i.e.,  $\leq 2\%$ ). We will initially exclude from the primary analysis those patients for whom postoperative troponin measurement was

not performed (for reasons other than death); as a sensitivity analysis, these patients will be then included and considered as not having MINS. For the primary analysis we will not include other covariates in the regression models. We will secondarily include the type of gynecological diagnosis/indication (based on our inclusion criteria) as covariate and as effect modifier.

As part of our secondary objectives, we will also evaluate the utility of frailty *when added* to the RCRI+age+MINS as predictors by calculating the net absolute reclassification improvement.

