(ECG) changes, is associated with a >3 fold increase in any-cause mortality within 30 day from surgery, with the highest attributable risk for death (34%) among all major postoperative complications. MINS is also strongly associated with mortality at 1 year. Embedding this evidence, the Canadian guidelines recommend a preoperative cardiovascular risk stratification that starts with calculating the RCRI; in those with a RCRI  $\geq 1$ , or with a RCRI=0 but 65 years old or older, troponin monitoring for the first 3 days after surgery is recommended.

These perioperative risk guidelines are followed in many centres in Canada and worldwide. However, this approach might have limitations in the GO population. Unpublished confidential data from VISION show that, among 271 women aged 55 or older undergoing major surgery for uro-gynecologic cancers, MINS was associated with a 2-to-3-fold increase in mortality at 1 year; however, those with no MINS (and not meeting the RCRI+age criteria for high risk) still had a 1-year mortality of 14% (compared to 3% in same age women in the overall VISION cohort without MINS). Limitations of the VISION study in order to inform our current practice with GO patients include: poor representation of this population; no collection of data on cancer-specific risk factors, and on preoperative and postoperative chemotherapy; no predictive ability for non-cardiac postoperative morbidity, and no intermediate time points (i.e. >30 days and <1 year). In addition, VISION did not include the assessment of patient reported outcomes (PROs), like QoL, functional recovery, or disability, which are poorly studied in the GO literature, but might be the most relevant to patients.

At no time does the current perioperative assessment of GO patients include frailty.

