## 2.3 Sample Size

The FARGO study is sized to respond to the primary objective. We expect a 20% rate of death or new disability at 6 months after surgery (primary outcome). We performed preliminary analyses of the VISION cohort, where data for women undergoing surgery for gynecologic cancer could not be distinguished from women undergoing surgery for urological cancer. Based on these analyses, we expect that, in our study population, the ability of the baseline RCRI+age combined with the occurrence of MINS to predict 6-month death or new disability, measured as Area Under the receiver operating characteristic Curve (AUC), will not be greater than 0.600 (range 0.550-0.600, Appendix I).

A sample size of 280 patients will give us at least 80% of power to detect a difference of at least 0.130 in the AUC for a model including only the FP-frailty assessment, compared with the AUC for the model including preoperative RCRI+age combined with MINS (i.e., AUC for FP-frailty model of at least 0.680^21). The table in the Appendix I shows the sample size calculation based on these assumptions for a range of scenarios, based on the comparison of 2 Receiving Operating Characteristic (ROC) curves, 2-sided test, alpha=0.05, and assumed correlation between the 2 predictive models=0.5.

We will include 280 patients in order to conservatively account for  $\leq 10\%$  of participants who will be lost before or during surgery, and in whom troponin measurement to assess for MINS will not be possible (in fact, we expect that after recruitment much fewer patients will not undergo or survive surgery). Based on our eligibility criteria, we expect that at least 50% (i.e., 140) of our participants will undergo chemotherapy, before and or after surgery, and will be included in our exploratory secondary analyses on chemotherapy outcomes.

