### **4.1 Primary clinical outcomes**

The primary outcome is all-cause death or new disability at 6 months after surgery. We will measure disability in several domains (including cognition, mobility, self-care, participation) using the 12-item World Health Organization Disability Assessment Schedule (WHODAS 2.0), a patient-reported outcome tool widely validated in surgical older populations. New disability will be defined as a disability score  $\geq 25\%$  at follow-up, or a score increase of  $\geq 8\%$  for those already disabled at baseline.

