# Appendices

## Appendix I. Sample size calculations

The sample size calculation is based on the comparison of two receiver operator characteristic curves (ROC), 2-sided test, with alpha=0.05. The assumed AUC for the RCRI, age, and MINS model is 0.55 (AUC1). The assumed AUC of the frailty assessment model is between 0.65-0.75 (AUC2). The assumed AUC difference is approximately 0.13. We expect an incidence of the primary outcome (all-cause death or disability at 6 months after surgery) to be 20%.

A sample size of 250 patients will give us at least 80% of power to detect a difference of at least 0.130 in the AUC for a model including only the FP-frailty assessment, compared with the AUC for the model including preoperative RCRI and age combined with MINS.

The assumed correlation between the two predictive models is 0.50 for the positive group (those experiencing the outcome) and 0.50 for the negative group (those not experiencing the outcome)

We will include 280 patients to conservatively account for ≤10% who will be lost before or during surgery, or in whom biomarker measurement will not be possible.

Software: PASS 13 (NCSS, LLC. Kaysville, Utah, USA. [www.ncss.com](http://www.ncss.com))

Sample size calculation

| AUC1 | AUC difference | AUC2 | Target power | Sample size |
|------|----------------|------|--------------|-------------|
| 0.55 | 0.10           | 0.65 | 80%          | 405         |
| 0.55 | 0.10           | 0.65 | 85%          | 465         |
| 0.55 | 0.10           | 0.65 | 90%          | 545         |
| 0.55 | 0.13           | 0.68 | 80%          | 240         |
| 0.55 | 0.13           | 0.68 | 85%          | 280         |
| 0.55 | 0.13           | 0.68 | 90%          | 325         |
| 0.55 | 0.15           | 0.70 | 80%          | 185         |
| 0.55 | 0.15           | 0.70 | 85%          | 210         |
| 0.55 | 0.15           | 0.70 | 90%          | 245         |
| 0.60 | 0.10           | 0.70 | 80%          | 425         |
| 0.60 | 0.10           | 0.70 | 85%          | 485         |
| 0.60 | 0.10           | 0.70 | 90%          | 570         |
| 0.60 | 0.13           | 0.73 | 80%          | 250         |
| 0.60 | 0.13           | 0.73 | 85%          | 290         |
| 0.60 | 0.13           | 0.73 | 90%          | 340         |
| 0.60 | 0.15           | 0.75 | 80%          | 190         |
| 0.60 | 0.15           | 0.75 | 85%          | 220         |
| 0.60 | 0.15           | 0.75 | 90%          | 255         |

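### The primary analysis drops everyone who dies by day 28, although those deaths are primary-outcome events, and no stated analysis of the primary AUC comparison restores them

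*Protocol*

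**What the plan says.** Section 4.1 of the protocol sets the endpoint: "The primary outcome is all-cause death or new disability at 6 months after surgery". The primary objective in 2.1.1 and the research question in 1.1 use the same composite in patients undergoing surgery. None of the three conditions on survival to any day.

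Section 6.1 then narrows the analysis set: "We will include in the primary analysis only study participants who are alive at 28 days after surgery". It adds: "We expect this will exclude from the primary analysis a very small proportion of patients initially enrolled in the study", put at 2% or less. No reason is given. The one sensitivity analysis named there concerns patients without a postoperative troponin.

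Section 2.3 and Appendix I size the study on a 20% rate of the full composite. Of the 280 patients, up to 10% are allowed for loss before or during surgery or for missing troponin or biomarker measurement. Deaths between surgery and day 28 are not named in that allowance.

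Two further places matter. Section 1.2.2 supports the use of MINS partly because it is "associated with a >3 fold increase in any-cause mortality within 30 day from surgery". Section 3.1.5 lets MINS accrue for 28 days after surgery begins.

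**The concern.** A patient who dies by day 28 has met the primary endpoint. Dropping that patient selects the analysis set on the outcome, and every record removed is an event. The result then describes death or new disability between day 28 and 6 months among early survivors, while the objective and the endpoint describe the whole period from surgery.

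Both predictors are affected. A preoperative frailty assessment is complete before surgery and is meant to foresee early death as well as later harm. MINS is put forward in part for its link with 30-day mortality, which is almost exactly the window removed. The protocol is also not uniform: section 6.2 keeps deaths in the disability-trajectory analysis by giving them the score of 100, while the primary analysis deletes early ones.

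At stake are whether the headline comparison answers the stated question, and whether the event count behind the sample size is the one that will be analysed.

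**Working it through.** **1. The plan's own sample size.** The inputs are from Appendix I: "2-sided test, with alpha=0.05", comparator AUC 0.55 (0.60 in the alternative scenario), "The assumed AUC difference is approximately 0.13", 20% events, correlation 0.5 in both outcome groups. I used the binormal variance for two correlated AUCs. With a = √2·Φ⁻¹(AUC), f = exp(−a²/4)/√(4π), g = −a·exp(−a²/4)/√(16π), and R non-events per event:

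- V = f²(1 + 1/R + a²/2) + g²(1 + R)/(2R)
- C = f₁f₂(r + r/R + r²a₁a₂/2) + g₁g₂r²(1 + R)/(2R) + f₁g₂r²a₁/2 + f₂g₁r²a₂/2, with r = 0.5
- V_A = V₁ + V₂ − 2C; V₀ is the same with both AUCs at the comparator value
- events needed = [(1.96√V₀ + 0.84√V_A)/0.13]²

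Results:

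- 0.55 vs 0.68: V₀ = 0.1010, V_A = 0.1087, giving 47.96, so 48 events and 48 × 5 = 240 patients.
- 0.60 vs 0.73: V₀ = 0.1051, V_A = 0.1135, giving 49.97, so 50 events and 250 patients.

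Both match the table. The same formula reproduces all 18 rows.

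**2. Events deleted at the 2% ceiling.** Expected events are 280 × 0.20 = 56. Early deaths are 280 × 0.02 = 5.6, and 5.6/56 = 10%. The remaining rate is (56 − 5.6)/(280 − 5.6) = 18.4%.

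**3. Power.** Power = Φ[(0.13√events − 1.96√V₀)/√V_A], with R reset to each case.

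| Case | Patients | Events | 0.55 vs 0.68 | 0.60 vs 0.73 |
|---|---|---|---|---|
| 10% loss, early deaths kept | 252 | 50.4 | 81.9% | 80.3% |
| 2% excluded, no other loss | 274.4 | 50.4 | 82.6% | 81.0% |
| 10% loss, then 2% excluded | 247.0 | 45.4 | 78.6% | 76.9% |
| Both losses, if 20% already describes survivors | 247.0 | 49.4 | 81.1% | 79.6% |

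The restriction costs 81.9 − 78.6 = 3.3 points, or 80.3 − 76.9 = 3.4. If all 5.6 deaths are taken from the 252, leaving 246.4 patients and 44.8 events, power is 78.2% and 76.5%, about half a point lower. With the full 2% excluded, power stays at or above 80% up to about 6.5% other loss for 0.55 vs 0.68, and up to about 2% for 0.60 vs 0.73. Holding 80% in the third case would need about 291 or 304 enrolled.

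**4. Shift in the comparator's AUC.** Section 3.1.5 makes the comparator a yes/no category, so AUC = (sensitivity + specificity)/2. The documents do not give the share p in the high-risk category, 28-day mortality m, or the early-death ratio k in this population. I assumed p = 10–20%, m = 1–2%, k = 3–5, and an overall AUC of 0.55–0.60.

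- Sensitivity − false-positive rate = 2·AUC − 1, and 0.20·sensitivity + 0.80·false-positive rate = p.
- Share of early deaths in the category: q = kp/(kp + 1 − p).
- Sensitivity after exclusion: (0.20·sensitivity − qm)/(0.20 − m). The AUC shifts by half the change.

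Largest fall (p = 20%, m = 2%, k = 5, AUC 0.55): sensitivity 0.280, q = 0.556, new sensitivity (0.0560 − 0.0111)/0.18 = 0.249, shift −0.015. Other extreme (p = 10%, m = 2%, k = 3, AUC 0.60): sensitivity 0.260, q = 0.25, new sensitivity (0.052 − 0.005)/0.18 = 0.261, shift +0.001. The design difference is 0.13.

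**The case against.** The best defence is that day 28 is a landmark. MINS may accrue until then, so starting the outcome clock when that predictor closes keeps its window equal for everyone. It also keeps MINS from being credited with a death it immediately precedes. That rationale is respectable, but the protocol does not state it, and the objective and endpoint are not worded as a landmark question. Scheduled troponin sampling stops at day 3 or discharge, and preoperative frailty needs no landmark at all. What stands is that the survivor analysis deserves a place as a sensitivity analysis.

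It is also fair to say that early deaths are not lost to the study. Section 4.2 lists 28-day and later mortality, and secondary objectives 5 and 6 cover them. But objective 5 uses RCRI and age without MINS, and nothing stated repeats the primary AUC comparison with early deaths included. A statistical analysis plan, not at hand here, might add one. It would still sit behind a primary set that the protocol fixes.

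Two stronger readings are tempting. A reader might infer that the rule breaks the stated power. It does not: the loss is a few points, the shortfall needs the exclusion at or near 2% plus other losses, and section 2.3 calls the 10% conservative. A reader might also infer that the rule tilts the comparison toward frailty. The documents do not support that either:

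- Frailty may also predict early death, so its AUC could fall too.
- The 34% attributable risk in 1.2.2 ranks MINS against other complications, not early against late death. The same section also links MINS to 1-year mortality.
- A lower comparator AUC would widen the difference and raise power, so both harms cannot be claimed together.

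**Conclusion.** The point holds as a mismatch between the stated question and the analysed population. The rule excludes on the outcome, removes up to about 10% of expected events, and has no stated counterpart that restores them. The size rests on the protocol's 2% ceiling and on reading 20% as the rate of the full composite. With fewer early deaths it shrinks in proportion.

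The power consequence is secondary: about 79% or 77% in the stacked worst case, and 80% or slightly above when other losses are small. The comparator's AUC may fall, by no more than about 0.015 under the assumed prevalences and risk ratios. The direction of any net bias in the AUC difference is undetermined.

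**What to change.** In section 6.1, define the primary set as all operated patients with at least one postoperative troponin. Count deaths to day 28 as events, with MINS as ascertained before death. Report the 28-day-survivor analysis as a landmark sensitivity analysis and give its reason. Keep the day-28 restriction for the dynamic analysis in 6.2, where the predictor is the 28-day frailty reassessment. Reword the exclusion for missing troponin so that patients who die before any measurement have a stated place; the existing sensitivity analysis that counts unmeasured patients as having no MINS can take them.

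In section 2.3 and Appendix I, state whether the 20% rate and the 10% allowance include deaths to day 28.

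The cost is about a paragraph in 6.1 and a sentence in each sample-size section, with no new data. The downside is that MINS is observed for a shorter time in the few early deaths and may closely precede some of them. The landmark sensitivity analysis shows whether that matters.

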## **6.2 Secondary Analyses**

To compare the predictive performance of different frailty assessments, we will use a similar approach as for the primary outcome, i.e., we will compare the c-statistics of logistic regression models, each including one type of frailty assessment.

To examine the added value of a dynamic perioperative frailty assessment on the primary outcome, we will use a logistic regression model including as predictor with preoperative frailty and change in frailty at 28 days after surgery (either as absolute change and as percent change). The association of frailty with trajectories of disability over the 1 year after surgery will be assessed in a repeated measures linear regression analysis (i.e., mixed effects model); participants who are no longer alive at follow-up will be assigned a score of 100.

Logistic regression or time-to-event models will be performed for the association of frailty and perioperative cardiovascular risk assessment with other outcomes, including chemotherapy-related outcomes, as appropriate.

Effects sizes (odds ratios or hazard ratios) will be presented together with 95% confidence intervals. The threshold for statistical significance will be set as  $p < 0.05$ .

The physicians' and patients' acceptability scores will be compared between frailty instruments using Wilcoxon signed rank tests. The mean and standard deviation (in seconds) required to complete each frailty instrument will be compared using Student t tests; the numbers of missing values will be compared using 2x2 tests.

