| Follow-up            | 
Follow-up visits will be done (either by phone or in person) at 28 days, 6 months, and 1-year post-surgery. Efforts will be made to perform these visits in concomitance with clinical follow-ups. Frailty assessments will be repeated at the
                                                                                                                                                                                                                                                                                                                                                                                                                                                                                                                                                                                                                                                                                                                                                                                                                                                                                                                                                                                                                                                                                                                 |

|  |                                                                                                                                                                                                                               |
|--|-------------------------------------------------------------------------------------------------------------------------------------------------------------------------------------------------------------------------------|
|  | 28-day visit. WHODAS 2.0 will be administered at the 28-day, 6-month and 1-year visits. MoCA will be administered at the 6-month and 1-year visits. Study personnel will evaluate all study outcomes at each follow-up visit. |
|--|-------------------------------------------------------------------------------------------------------------------------------------------------------------------------------------------------------------------------------|

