#### 3.1.1 *Frailty Phenotype*

Frailty will be measured based on the FP evaluation. The FP assessment is based on the following 5 criteria: weak muscle strength (decreased grip strength measured with a dynamometer), slow gait speed (measured on the 15-ft walking test), unintentional weight loss (> 10 lbs), exhaustion (self-reported), and low physical activity (low weekly energy expenditure). The patient receives 1 point for each criterion met, for a total score of: 0 to 1, not frail; 2 to 3, intermediate frail (pre-frail); 4 to 5, frail. The frailty status based on these categories will be evaluated as exposure for the primary research question. The actual FP score (i.e., from 0 to 5) and the score upon each of the components of the FP assessment will be secondarily evaluated as exposures/predictors. With an exploratory intent, at the first study FP assessment, the level of physical activity will be evaluated with regards to two different time point, i.e., the current level (which is what will enter the FP scoring for the purpose of the study objectives), and the usual level (before the diagnosis of cancer was made, or before the cancer likely started affecting their performance and lifestyle).

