## **5. FOLLOW UP**

### **5.1 Overall study**

Figure 2 shows the study participant timeline.

At baseline (i.e. before surgery, or before NACT for some cases), trained research personnel will collect relevant data about participant demographics, clinical and social history; will administer the WHODAS 2.0 questionnaire and the MoCA; and will assess for frailty. A trained clinical research assistant will measure frailty, first based on the CFS, and then administering the FP tests/questions. In patients undergoing NACT, the study personnel will repeat the frailty, WHODAS 2.0, and MoCA assessments before surgery, after the NACT is deemed to be terminated.

Study personnel will follow patients throughout their time in hospital for surgery, reviewing their medical records and recording any clinical outcome. In hospital, all patients will have troponin measured postoperatively, and then on the 1st, 2nd, and 3rd day after surgery or until discharge, whichever comes first. Data on ischemic symptoms/signs will be collected, and an ECG will be

performed if an elevated troponin measurement is detected. Data on any other troponin measurement that will be undertaken in any study participant within 28 days from surgery will be also collected and will be assessed upon the study definition for MINS. In hospital, study personnel will administer the 3D-CAM twice a day, during the first 3 days after surgery or until discharge, whatever comes first. We will use the CAM-ICU while the patients are in the Post-Anesthesia Care Unit (PACU) or if sent to ICU.

A follow-up study visit will be done at 28 days, 6 months, and 12 months after surgery. Efforts will be made to perform such study visits in concomitance with clinical follow-ups. Frailty assessments will be repeated at 28 days. WHODAS 2.0 will be administered at 28 days, 6 months and 12 months, in-person or over the phone, by research personnel blinded from the frailty assessments. MoCA will be administered at 6 and 12 months (in-person or through videoconference). Study personnel will also collect clinical outcome data through the study follow-ups.

We will also assess physicians' and patients' acceptability of frailty assessments (Appendix III).

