| Cognitive Assessment (MoCA)                   | X                                     | X                                  | X                                 |                        |                           | X                          | X                         |
| Troponin Measurement                          |                                       |                                    |                                   | X                      |                           |                            |                           |
| Disability Assessment (WHODAS 2.0)            | X                                     | X                                  | X                                 |                        | X                         | X                          | X                         |
| Delirium Assessment (3D-CAM)                  |                                       |                                    |                                   | X          |                           |                            |                           |
| Clinical Outcomes                             |                                       |                                    |                                   | X                      | X                         | X                          | X                         |
| Neoadjuvant Chemotherapy-related outcomes     |                                       |                                    | X                                 |                        |                           | X                          |                           |
| Blood Drawing for Biobanking                  | X                                     | X                                  | X                                 |                        | X                         | X                          | X                         |

 Should be done within 45 days prior to surgery  
 Refers to the round of chemotherapy closest to the surgery date  
 Should be done within 30 days prior to chemotherapy  
 Should be done at least 18 days post-chemotherapy cycle and within 45 days prior to surgery  
 Can be done in-person or by telephone/videoconference  
 Should be done twice a day

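### Percent change in the Frailty Phenotype score is undefined when the preoperative score is 0, and the permitted remote 28-day visit cannot yield a complete score

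*Protocol*

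**What the plan says.** Secondary objective 1b (section 2.1.2) compares a dynamic frailty assessment, repeated 28 days after surgery, with other frailty assessments as predictors of death or new disability at 6 months. Section 6.2 gives the model: logistic regression on preoperative frailty and "change in frailty at 28 days after surgery (either as absolute change and as percent change"). It compares frailty assessments through the c-statistics of their models.

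Section 3.1.1 describes the scale as "The actual FP score (i.e., from 0 to 5") and groups it "for a total score of: 0 to 1, not frail; 2 to 3, intermediate frail (pre-frail); 4 to 5, frail". Two of the five criteria are physical measurements: "weak muscle strength (decreased grip strength measured with a dynamometer), slow gait speed (measured on the 15-ft walking test"). Section 3.1.2 allows either FP or CFS, which runs from 1 to 9, to serve as the dynamic predictor.

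On visit mode, the Study Summary states: "Follow-up visits will be done (either by phone or in person) at 28 days, 6 months, and 1-year post-surgery". Figure 2 lists FP and CFS at the 28-Day Visit, and its footnote 5, attached to that column, reads "Can be done in-person or by telephone/videoconference". Section 5.1 says "Frailty assessments will be repeated at 28 days" and gives no mode for this, whereas it does give a mode for WHODAS 2.0 (in person or by phone) and for MoCA (in person or by videoconference).

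**The concern.** There are two separate defects, and both bear on objective 1b.

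The first is a denominator. Zero is a legitimate FP score, and the protocol has no rule for a percent change that starts from it. Ordinary regression software would drop those rows. The loss is selective, because only patients meeting no frailty criterion at baseline are removed, and these are patients in whom frailty appearing after surgery would be informative. A c-statistic from the remaining patients cannot be set beside one from a preoperative-only model fitted to everyone, since both the predictor and the population have changed.

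The second is measurement. A visit held by phone cannot supply grip strength by dynamometer or a timed 15-ft walk, and the protocol describes no remote version of either. Every FP change score, absolute or percent, needs the complete 28-day FP. An item not measured at 28 days cannot be recovered later, so an analysis plan written afterwards cannot repair the gap.

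**Working it through.** The protocol states no figure of its own on this point, so there is none to reproduce. The inputs are the FP range 0 to 5 and its categories (section 3.1.1), the change terms (section 6.2), the visit mode (Study Summary and Figure 2), and 250 evaluable patients with a 20% outcome rate (Appendix I). The share with preoperative FP of 0 and the share of remote 28-day visits are not given; 10% to 50% is assumed for each.

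**1. Where percent change is defined.** Percent change = 100 × (FP at 28 days − preoperative FP) / preoperative FP. There are 6 × 6 = 36 possible score pairs. The 6 pairs with a preoperative score of 0 have a zero denominator and are undefined. Absolute change is defined for all 36. For CFS the smallest denominator is 1, so percent change always exists.

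**2. Scaling where it is defined.** Each criterion is worth one point, yet worsening by one criterion becomes:
- 1 to 2: 100 × 1/1 = +100%
- 2 to 3: 100 × 1/2 = +50%
- 4 to 5: 100 × 1/4 = +25%

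**3. Size of the loss from the FP percent-change model.**
- 10% with FP of 0: 250 × 0.10 = 25 lost and 225 left, with about 225 × 0.20 = 45 events.
- 50% with FP of 0: 250 × 0.50 = 125 lost and 125 left, with about 125 × 0.20 = 25 events.

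The event counts apply the 20% rate uniformly. If patients with FP of 0 have fewer events than the rest, fewer events would be lost.

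**4. What a remote visit can score.** Without grip and gait, 5 − 2 = 3 items remain. Two outcomes are possible:
- *FP set to missing.* The patient leaves every FP-change model. At 10% to 50% remote visits, 250 × 0.10 = 25 to 250 × 0.50 = 125 patients lack a complete 28-day FP.
- *Available items summed.* The score cannot exceed 3, so the frail category (4 to 5) is out of reach. A preoperative 5 falls to at most 3 (−2, or −40%) and a preoperative 4 to at most 3 (−1, or −25%) with no real improvement.

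The groups in steps 3 and 4 may overlap, so their counts should not be added.

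**5. What survives without percent change.** A model with preoperative score P and absolute change (F − P), where F is the 28-day score, has linear predictor a + bP + c(F − P) = a + (b − c)P + cF. This is the model with P and F entered separately. Fitted risks and c-statistic are identical, so either form can be used.

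**The case against.** The strongest reply is that little of the dynamic analysis fails. Section 6.2 already plans absolute change alongside percent change, with preoperative frailty in the model, and section 3.1.2 allows a CFS version that has no zero denominator and needs no device. This stands. A reader might infer that the dynamic predictor as a whole breaks down, or that objective 1b loses its robust patients; the documents do not support that. Only FP of 0 is lost, although the not-frail category covers 0 to 1, and only from the FP percent-change version.

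A second reply is that footnote 5 describes whole visits and not procedures. The same 28-day column lists blood drawing, which no phone visit can provide, so the footnote cannot mean that every listed item may be done remotely. Visits are also meant to coincide with clinical follow-up where possible. This weakens any claim that remote FP is intended, but it does not settle the mode. Blood is taken only from those who give separate biobank consent (section 5.2), alignment with clinic visits is an aim and not a requirement, and section 5.1 is silent on the mode for frailty.

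A third reply concerns scoring. A reader might infer that every frail patient seen by phone will be misclassified as improved. That needs a partial-sum rule, which the protocol never states. Section 4.3 tracks completion of the FP and its sub-items, and section 6.2 compares numbers of missing values, which suggests that unperformed items will be recorded as missing. Missing data is therefore the likelier outcome, and false improvement is conditional. Nor do the documents show that patients seen remotely would be sicker, so no direction of bias can be claimed.

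**Conclusion.** Both defects stand in limited form. FP percent change is undefined at a preoperative score of 0 by the protocol's own scale, and it weights equal worsening unequally; this follows from the definitions and needs no assumption. The visit-mode conflict is also real on the text: a remote 28-day visit is allowed, FP is due at it, two of five items need physical measurement, and nothing requires attendance or says how an incomplete FP is handled.

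The size is uncertain. The figure of 25 to 125 of 250 patients for each problem rests wholly on the assumed 10% to 50% shares. The first problem is confined to the FP percent-change version. The second reaches any FP-change version, but only for patients seen remotely. The primary analysis uses preoperative FP and is untouched. The point is worth correcting because it affects a named secondary objective and because a 28-day FP that was not measured cannot be obtained afterwards.

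**What to change.** In section 6.2, delete percent change for FP and keep the preoperative score plus absolute change, or equivalently the preoperative and 28-day scores. State that static and dynamic models are compared in the same patients, namely those with both FP assessments. A likelihood-ratio test of the added 28-day term is an option but not essential.

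Reconcile the Study Summary, section 5.1 and Figure 2 footnote 5 with section 3.1.1: exempt FP from the remote option so that the 28-day FP is taken in person, ideally at the clinical follow-up already intended. When the visit has to be remote, record CFS and set FP to missing, never to a sum of the available items.

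The cost is a few words in section 6.2, a footnote to Figure 2 and matching text in the Summary and section 5.1. The downside is some missing 28-day FP values, with CFS as the fallback.
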